**Fig. 4 Fig4:**
[figure not shown]
Example signed quarterly feedback (simplified to fit into one page)

#### Methods for tailoring interventions

PHMA uses comprehensive approaches in tailoring interventions to the need and context of individual patients. First, PHMA requires that the intervention for any specific patient in any specific time period focuses on only one most important and feasible objective behavior or behavior problem determined by a priority score. This score is automatically generated by a computerized algorithm based on data accumulated from previous SMC with the patient and his/her self-monitored data. Second, each item in the IEC materials pool of PHMA is designed as a template inserted with variables to be replaced with relevant values, text or diagrams according to the actual conditions/contexts of the patient under concern. The following is a “template” message: *“{CustomerDemographics.FullName}**: **Capping monthly salt intake is an effective way in controlling blood pressure. You have {CustomerDemographics.FamilyMember. Number} members living together. So, your family should consume less than {ObjectiveBehavior.HealthyDiet.MonthlyFamilySalt} grams of salt a month in total.”* As indicated by “{}”, this message contains three variables. When sent to a patient named “Zhang San” who has 3 family members (two adults and a child of 8 years), the message is changed into: *“Zhang San**: **Capping monthly salt intake is an effective way in controlling blood pressure. You have 3 members living together. So, your family should consume less than 180 g of salt a month in total.”* Fig. 5 shows the template of the quarterly signed feedbacks mentioned earlier and Fig. 4 is an example feedback generated from this template.

**Fig. 5 Fig5:**
[figure not shown]
Template signed quarterly feedback

#### Variables for characterizing patients

PHMA maintains a growing pool of variables for characterizing individual patients. All these variables are classified, coded and computerized in a way that they can be easily: (a) added to relevant IEC templates in intervention development; and (b) replaced, in intervention implementation, with relevant values, text or images according to available data about the specific patient under concern. By the time this paper is written, a total of ten categories and over 300 of variables had been computerized. Table 1 presents all the categories identified so far and example variables under each category.

**Table 1 Tab1:** Categories and examples of variables used to tailor interventions

Demographics of patients (CustomerDemographics)
- Patient’s full name (CustomerDemographics. FullName);
- Patient’s Sex (CustomerDemographics.Sex);
- Patient’s Family name (CustomerDemographics. FamilyName);
……
Status and trend of blood pressure (BPPerformance)
- Overall mean of SBP (BPPerformance.SBP.Mean.Overall);
- Mean of SBP for the last 10 times (BPPerformance.SBP..Mean.Last10Times);
- Overall trend of DBP in past year (BPPerformance.DBP.Trend.LastYear);
……
Patient outcome (PatientOutcome)
- Score of quality of life (EQ5D) as assessed last time (PatientOutcome.QoL.LastAssessment.Score);
- Date when quality of life was last assessed (PatientOutcome.QoL LastAssessment.Date);
- Complications occurred in the past year (PatientOutcome.Complications.LastYear. All);
……
Clinical history in relation to hypertension (ClinicalHistory)
- Year in which hypertension was diagnosed (ClinicalHistory.Hypertension.Diagnosis.Year);
- Whether medication treatment is in use (ClinicalHistory.Hypertension.Treatment.Current.Status);
- Type of current medications (ClinicalHistory.Hypertension.Treatment.Current.Type);
……
Objective behaviors (ObjectiveBehaviors)
- Title of the objective behavior scored the highest in previous assessment (ObjectiveBehaviors.LatestAssessment. ScoredHighest.Title);
- Score of “healthy diet” in the latest assessment (ObjectiveBehaviors.LatestAssessmen.HealthyDiet.Score);
- Title of objective behavior scored the least in latest assessment (ObjectiveBehaviors.LatestAssessment. ScoredLeast.Title);
……
Problems with or barriers to objective behaviors (BehaviourProblems)
- List of problems or barriers identified from the latest assessment (BehaviourProblems.LatestAssessment.FullList);
- Title of problem scored the highest in the latest assessment (BehaviourProblems.LatestAssessment. ScoredHighest.Title); - Description of problem scored the highest in the latest assessment (BehaviourProblems.LatestAssessment. ScoredHighest.Description); ……
Hypertension-related physical indicators (PhysicalIndicator)
- Body weight as measured last time (PhysicalIndicator.BodyWeight.LastMeasurement.Value);
- Date when patient body was last weighted (PhysicalIndicator.BodyWeight.LastMeasurement.Date);
- Waist circumference as measured last time (PhysicalIndicator.WeistCircumference.LastMeasurement.Value);
……
Daily activities (DailyActivity)
- Common working activities as reported last time (DailyActivity.LastReport.Work.Description);
- Common working hours as reported last time (DailyActivity.LastReport.Work.Hours);
- Common leisure activities as reported last time (DailyActivity.LastReport.Leisure.Description);;
……
Social relations (SocialRelations)
- Number of family members (SocialRelations.FamilyMember.Number);
- Member of family members (SocialRelations.FamilyMember.RelationList);
- Family member in closest contact with the patient (SocialRelations.FamilyMember.InClosestContact.Relations);
……
Resources relating to hypertension management (Resources)
- Family income per year (Resources.Faimly.AnnualIncome)
- Minutes needed to get to the nearest hypertension clinic (Resources.MinutesToNearestClinic);
- Name of doctor in charge of the patient (Resources.DoctorInCharge.Current.FullName);
……

“()” defines the start and end of the code of the variable or variable category before it

### Study design and settings

The study adopts a cluster randomized controlled trial (RCT) design involving a total of 60 site communities with 12 in the control arm and 48 in the intervention arm. The control arm maintains existing hypertension case management; while the intervention arms, personalized hypertension management as described above. Project evaluation applies to both arms using the same data collection methods and by same field data collectors. The uneven distribution of site communities between the control and intervention arms was designed to enable detection of potential differences between the control arm and at least four main subgroups with different intervention ingredients within the intervention arm. The analysis and reporting of the trial will strictly follow the CONSORT guidelines [29, 30]. A Trial Steering Committee has been established which holds annual meetings and supervises the trial implementation. For time schedule of the trial please refer to Additional file 1.

### Selection and randomization of communities

The RCT is implemented in Anhui, an inland province located in eastern China with a population of about 70 million living in 105 cities or counties. Selection of participating sites and patients uses a clustered randomization which proceeds in the following steps: step1 divides Anhui province into north, middle and south regions; step 2 randomly selects 4 cities/counties from each of the three regions; step 3 randomly selects five non-adjacent communities from each of the cities/counties selected; step 4 randomly selects 56 patients diagnosed with hypertension from the communities selected. The five communities selected from each city/county in steps 3 are randomly assigned to the control arm (n = 1) and intervention arm (n = 4). Hypertensive patients aged 18 years or above and capable and willing to participate in the study from the selected communities meet the inclusion criteria. All the randomization is performed by a statistical professional from outside the project team. The study will be blinded to both data collectors and analyst.

### Withdrawal

Any participant can withdraw from the study at any time. The participants withdrawn from the study will not be replaced but the withdrawal reasons will be recorded.

### Study sample size

The above sample size of participating patients is calculated on base of the primary intervention assessment measures, i.e., changes in SBP. Based on our previous study results and our aim of comparing the effects of at least four combinations of main intervention ingredients, we suppose: (a) SBP reduction was about 5.0 mmHg as compared between the intervention and control arms; (b) standard deviation of the SBP reduction was 7.8 mmHg; (c) ICC value was 0.05; and (d) patients in the intention arm need to be assigned to four subgroups to receive four different combinations of interventions. So, to detect a possible absolute difference of 5.0 mmHg with 90% power and alpha 0.05, we need 228 patients in each arm. By allowing for a 20% attrition rate and a design effect of 2.45, the total sample size is estimated as 3352 (= 2.45 * 228 * 5 * 1.2) and this translates into 56 patients per community.

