## Measures

The primary measures for assessing the efficacy of PHMA are SBP/DBP. The secondary measures include quality of life (EQ5D-5L), hypertension-related complications, healthcare utilization and objective behaviors.

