### Data analysis

The data collected will be used to compare the differences between the control groups and the intervention group as a whole and subgroups with different intervention ingredients in the intervention arm at different time points in terms of: (a) SBP/DBP; and (b) the secondary measures including quality of life, occurrence of hypertension-related complications, healthcare utilization, and scores of objective behaviors. Estimation of statistical significance and confidence intervals will assume a type I error established in alpha = 0.05, using the IBM SPSS V22 statistics package. Despite our anticipated high follow-up rates, we expect some extent of missing data, typically participants missing an interview and are then found at the next follow-up assessment. We will use appropriate statistical techniques to estimate the missing values and then perform the analysis on the completed sample.

Initial data analysis will consist of descriptive summaries intended to examine the patterns of the various measurements and check for normality of the continuous variables. Necessary transformations will be explored and selected, if necessary, to induce approximate normality. Regarding the numerical variables between two groups, t-test of independent samples for mean comparisons will be carried out. We will also employ generalized hierarchical linear models. These models will include multiple linear regression, as well as binary, ordinal, or nominal logistic regression. In these multilevel analyses, patient-specific measurements are included in the models.

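### The trial is sized on change in SBP, but the primary comparison is stated on SBP/DBP levels and its one named test uses no baseline BP

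*Protocol article*

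**What the plan says.** Under Study sample size, the article describes the calculation as "calculated on base of the primary intervention assessment measures, i.e., changes in SBP". The inputs are on that scale: "SBP reduction was about 5.0 mmHg as compared between the intervention and control arms" and "standard deviation of the SBP reduction was 7.8 mmHg". It gives no SD for SBP at a single visit and no correlation between baseline and follow-up.

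The other sections do not mention change. Measures states: "The primary measures for assessing the efficacy of PHMA are SBP/DBP". The hypothesis under Aim/objectives is that BP will be lower in the intervention arm. Data analysis compares the arms "at different time points in terms of: (a) SBP/DBP".

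For numerical variables in two groups, Data analysis names an independent-samples t-test. It then adds hierarchical models, and the only thing said there about their content is: "In these multilevel analyses, patient-specific measurements are included in the models". Those measurements are not listed. Data collection and management says BP is measured at baseline, 12 and 24 months, and that potential confounders such as age, sex, education and years since diagnosis are also collected.

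**The concern.** The SD of 7.8 mmHg belongs to a within-patient change. It does not describe SBP at one visit, which carries the full spread between patients. A reader who takes the sizing section and the analysis section together cannot tell whether the primary result will be a difference in change, in unadjusted level, or in level adjusted for baseline. These have different variances, and the choice could be made after the data are seen.

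The only test named outright has no baseline term. Applied to follow-up SBP, it gives up the precision that the collected baseline value offers. It also leaves in the estimate whatever chance difference in baseline SBP exists between 12 control and 48 intervention communities. Both matter against a target difference of 5.0 mmHg.

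**Working it through.** **The plan's own figure.** With difference 5.0, SD 7.8, two-sided alpha 0.05 (sidedness is not stated) and 90% power:

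n per arm = 2 × (1.960 + 1.282)² × 7.8² / 5.0² = 51.1, so 52.

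The article says "with 90% power and alpha 0.05, we need 228 patients in each arm". The 228 is not reproduced from the stated inputs; it would need an SD of about 16.5 mmHg or a difference of about 2.4 mmHg. The last step does reproduce: 2.45 × 228 × 5 × 1.2 = 3351.6, so 3352. The 228 discrepancy is a separate matter and is used here only under the objection.

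**Inputs for the check.**
- From the document: change SD 7.8; "ICC value was 0.05"; 12 control and 48 intervention communities; 56 patients per community; 20% attrition, so 56 × 0.8 = 44.8 completers per community.
- Assumed: equal SBP variance at baseline and follow-up; ICC 0.05 on every scale; baseline/follow-up correlation ρ from 0.5 to 0.9; separately, a level SD of 14 to 20 mmHg.

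**Step 1: variance by type of analysis.** From SD_change² = 2(1 − ρ) × SD_level²:
- SD_level = 7.8 / √(2(1 − ρ))
- SD_adjusted = SD_level × √(1 − ρ²)
- variance ratio, level to adjusted = 1 / (1 − ρ²)
- variance ratio, level to change = 1 / (2(1 − ρ))

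| ρ | SD level | SD adjusted | level / adjusted | level / change |
|---|---|---|---|---|
| 0.3 | 6.6 | 6.3 | 1.10 | 0.71 |
| 0.5 | 7.8 | 6.8 | 1.33 | 1.00 |
| 0.7 | 10.1 | 7.2 | 1.96 | 1.67 |
| 0.8 | 12.3 | 7.4 | 2.78 | 2.50 |
| 0.9 | 17.4 | 7.6 | 5.26 | 5.00 |

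The level is less precise than the adjusted analysis at every nonzero ρ. It is less precise than change only when ρ exceeds 0.5.

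**Step 2: chance baseline difference, 12 v 48 communities.** SE = SD_level × √[(0.05 + 0.95/44.8) × (1/12 + 1/48)] = 0.0861 × SD_level. This gives 0.67 mmHg at ρ = 0.5, 1.06 at 0.8 and 1.50 at 0.9.

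**Step 3: precision of the whole-arm comparison.** Design effect = 1 + 43.8 × 0.05 = 3.19. SE = SD × √[3.19 × (1/537.6 + 1/2150.4)] = 0.0861 × SD, and the 95% half-width is 2.00 × SE (t with 58 degrees of freedom).

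| SD | SE | half-width | power for 5 mmHg |
|---|---|---|---|
| 7.8 | 0.67 | 1.3 | above 99% |
| 14 | 1.21 | 2.4 | 98% |
| 16 | 1.38 | 2.8 | 95% |
| 20 | 1.72 | 3.4 | 81% |

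A level SD of 14 to 20 with a change SD of 7.8 implies ρ = 1 − 7.8²/(2 × SD²), that is 0.84 to 0.92. The baseline-adjusted SD would then be 7.5 to 7.7, which brings the half-width back to about 1.3 mmHg.

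**The case against.** The strongest reply is that this is a mismatch of wording. Under randomisation, the difference between arms in follow-up SBP and the difference in change have the same expected value, and the hypothesis fits either. That stands: the issue is variance and clarity, and the effect being tested is the same.

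Several stronger readings are tempting, and the document does not support them.

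- *The models leave out baseline BP.* The article does not say so. The unnamed patient measurements could include it, and an exact covariate list is commonly left to a fuller document. The t-test sentence also sits in the paragraph on initial analysis and is not labelled primary. But no sentence makes the model primary either, and the t-test is the only test named.
- *The models adjust for measures taken after randomisation.* The wording does not limit covariates to baseline. However, the confounders listed under Data collection and management are age, sex, education and years since diagnosis, while behaviours and healthcare use are listed as outcomes. Confounder adjustment is the natural reading.
- *Baseline imbalance biases the result.* One control and four intervention communities are randomised within each city or county, so what remains is chance. A cluster-aware interval for the level already covers that chance variation; it is the same loss as the wider interval and should not be counted twice.
- *The trial is underpowered because of the mismatch.* Whole-arm power on the level stays at 95% or more up to SD 16. The 228 per arm would itself give 90% power, before clustering, at an SD of about 16.5. For control against one subgroup of 12 communities (equal subgroups assumed), power on the level is 88%, 78% and 59% at SD 14, 16 and 20 with design effect 3.19. With the stated 2.45 it is 95%, 88% and 71%. So part of that shortfall comes from the design effect and cannot be charged to the endpoint mismatch alone.

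**Conclusion.** The point holds in a limited form. The sizing section and the analysis sections describe the primary measure differently, the 7.8 mmHg SD fits only the former, and the one named test makes no use of a baseline value that is collected.

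The gain from adjustment follows from the algebra at any nonzero correlation, given equal variances at the two visits. Its size depends on a correlation, or equivalently a level SD, that the document does not give. The half-width would almost double at an assumed level SD of 14 mmHg and be about 2.6 times as wide at 20 (3.4/1.3). At a correlation near 0.5 an unadjusted level would be no worse than change and only a third more variable than the adjusted analysis. The figures also assume an ICC of 0.05 on each scale and 20% attrition. This should be corrected, but it does not show that the main comparison is biased or that the trial is too small.

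**What to change.** Define the primary endpoint once: SBP (and DBP) at a named follow-up visit, compared between arms in the multilevel model with a community effect and the patient's own baseline SBP (or DBP) as covariate. State that this model is the primary comparison and that the t-test is descriptive at most. Name the other covariates as baseline values, for example the confounders already listed under Data collection and management; this removes any doubt about what the patient measurements are.

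Then align Study sample size, Measures and Data analysis with that definition, and say which SD the calculation uses (level, change or baseline-adjusted) with the correlation behind it.

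Baseline BP is already measured, so no visit, measurement or patient is added. The cost is wording in the protocol and analysis plan, settled before outcome data are examined.

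### The 228 patients per arm do not follow from the stated inputs, which give 52, so the 3352 total and the 90% power are not derived from the printed assumptions

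*Protocol article*

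**What the plan says.** In the protocol article, under Study sample size, the calculation is based on change in SBP. The assumptions are a reduction of about 5.0 mmHg between arms, that the "standard deviation of the SBP reduction was 7.8 mmHg", that the "ICC value was 0.05", and that "patients in the intention arm need to be assigned to four subgroups to receive four different combinations of interventions". From these the article concludes that "with 90% power and alpha 0.05, we need 228 patients in each arm". It then multiplies 228 by a design effect of 2.45, by 5 groups and by 1.2 for 20% attrition. The result is 3352 patients, or 56 in each of 60 communities.

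The Data analysis section says that significance testing "will assume a type I error established in alpha = 0.05". It mentions no division of alpha across comparisons.

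**The concern.** The article prints every input to the unadjusted per-arm number and then a result that those inputs do not give. This is a mismatch between printed figures, not a detail left to another document. Every later size figure is a multiple of 228: the 3352 total, the 56 per community and the attached claim of 90% power. If 228 has another source, the SD, difference, alpha or power on the page is not the one that was used. A reader then cannot tell what effect the trial was sized to detect.

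**Working it through.** **Inputs** (Study sample size): difference 5.0 mmHg; SD of the reduction 7.8 mmHg; power 90%; alpha 0.05. Sidedness is not stated; two-sided is assumed, and one-sided was also tried.

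**The plan's own product.** 2.45 × 228 × 5 × 1.2 = 3351.6, which rounds to 3352, and 3352 / 60 = 55.9, or 56 per community. These steps reproduce. They also show that clustering, attrition and the number of groups are applied after 228, so 228 is the unadjusted per-group number.

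**The 228 itself.** n = 2 × (1.960 + 1.2816)² × 7.8² / 5.0² = 2 × 10.507 × 60.84 / 25 = 51.1, so 52 per arm. The t-based calculation gives 52.1, so 53. The ratio is 228 / 52 = 4.4. Carrying 52 through the same multipliers gives 2.45 × 52 × 5 × 1.2 = 764.

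**Power at 228.** With 228 independent patients per arm, the standard error is 7.8 × √(2/228) = 0.730 and 5.0 / 0.730 = 6.84. Power is above 99.99%, not 90%.

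**Variants keeping 5.0 mmHg and SD 7.8 (90% power)**

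| Variant | Per group |
|---|---|
| One-sided alpha 0.05 | 42 |
| 4:1 allocation | 32 control, 128 in the larger arm |
| Bonferroni for 4 / 10 / 20 contrasts | 70 / 82 / 91 |
| SD multiplied by √2 | 103 |
| SD multiplied by √2, Bonferroni for 4 / 10 / 20 | 140 / 163 / 181 |
| Five-group ANOVA, several mean patterns | about 31 to 76 |
| 52 × 4 subgroups | 208 |

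None gives 228. The nearest is 52 × 3.75 × 1.2 = 234, where 3.75 = 1 + 55 × 0.05 is the design effect for 56 per community. It is not 228 either, and it would count clustering and attrition twice.

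**What 228 would need at alpha 0.05 and 90% power.** SD / difference = √(228/2) / 3.2415 = 3.29. Changing one input at a time, that is SD 5.0 × 3.29 = 16.5 mmHg, or a difference of 7.8 / 3.29 = 2.4 mmHg.

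**Power of the fixed design.** Take 56 × 0.8 = 44.8 analysed per community and ICC 0.05. The design effect is 1 + 43.8 × 0.05 = 3.19. Effective numbers are 12 × 44.8 / 3.19 = 168.5 for control and 48 × 44.8 / 3.19 = 674.1 for intervention.

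- Pooled, 48 v 12: √(1/168.5 + 1/674.1) = 0.0861. At SD 7.8 the standard error is 0.672, power for 5.0 mmHg is above 99.9%, and the difference detectable with 90% power is 3.2415 × 0.672 = 2.2 mmHg. At SD 16.5 the standard error is 1.421 and power for 5.0 mmHg is about 94% (93% with t on 58 df).
- One subgroup v control, **assuming 12 communities per subgroup**: √(2/168.5) = 0.1089. At SD 7.8 the detectable difference is 3.2415 × 0.850 = 2.8 mmHg. At SD 16.5 power for 5.0 mmHg is about 80% (76% with t on 22 df), and the detectable difference is 5.8 mmHg.

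**The case against.** The strongest reply is that the discrepancy is conservative. On the printed inputs the trial enrols several times what it needs. Even with the full cluster penalty, power for 5.0 mmHg exceeds 99.9%, and no recruitment figure, allocation or analysis has to change. That is right. A reader might infer from the mismatch that the trial is underpowered, but the documents do not support this. The SD of 16.5 is a back-calculation with no source in the article.

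A second reply is that 228 may come from a smaller contrast between ingredient combinations, perhaps with a divided alpha. The section does cite the aim of comparing at least four combinations. Such routes exist. At SD 7.8, a 2.5 mmHg difference with two-sided alpha 0.01 and 80% power gives 228, and 3.0 mmHg with alpha 0.005 and 90% power gives 227. It would therefore be wrong to say that 228 fits only SD 16.5 or a difference of 2.4 mmHg. But the article states none of these inputs. It ties 228 to 5.0 mmHg, 90% power and alpha 0.05.

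A third reply is that the subgroup layout is not fixed. Communities are "randomly assigned to the control arm (n = 1) and intervention arm (n = 4") within each city or county, while the sample-size section speaks of patients being assigned to subgroups. Twelve communities per subgroup is therefore an assumption, and every subgroup figure here depends on it. This objection stands in full. The pooled figures do not depend on it.

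A reader might also infer that a null or small result could not be interpreted. That does not follow. The result would be read from its estimate and confidence interval, which use the observed SD and ICC, not the planning values.

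**Conclusion.** The point holds as an arithmetic contradiction. With the printed difference, SD, power and alpha, the unadjusted requirement is 52 per arm (53 with the t correction), not 228. The reading as two-sided is an assumption, but one-sided gives 42 and moves further away. The 3352 total and the 90% power therefore do not follow from the stated assumptions.

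The direction on those assumptions is toward too many patients. What remains unknown is whether the SD and difference on the page are the ones used. If they are, 90% understates the power of the design. If the SD was in fact nearer 16.5, 90% would be roughly met for the pooled comparison but, with 12 communities per subgroup, missed for each subgroup contrast. The article gives no means of choosing between these. The correction should still be required, because the sample-size statement for the primary outcome is wrong as written and cheap to put right.

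**What to change.** Trace 228 to its source and print the SD, difference, alpha, sidedness and power that produce it. Keep the enrolled number; nothing here calls for adding or removing patients.

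- If SD 7.8 and 5.0 mmHg stand, state 52 as the per-arm requirement before inflation. Justify 3352 by what the fixed design delivers: above 99.9% power for 5.0 mmHg pooled, or 90% for about 2.2 mmHg. Simply putting 52 into the printed product would give 764 and leave 3352 without a basis.
- If another SD or difference was used, print it with the power it gives. At SD 16.5, for example, that is about 94% pooled.
- State how the four subgroups are formed before quoting any subgroup power. With 12 communities each, 90% power is reached at about 2.8 mmHg for SD 7.8, and power for 5.0 mmHg is about 76 to 80% for SD 16.5.

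The cost is a rewritten sample-size paragraph and a changed statement of power or detectable difference.

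### The sample-size derivation uses a design effect for 30 patients per community where 56 are enrolled, and under-inflates for attrition; whether power is lost depends on an unreconciled standard deviation

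*Protocol article*

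**What the plan says.** The Study sample size section of the Protocol article assumes that "SBP reduction was about 5.0 mmHg as compared between the intervention and control arms", that "standard deviation of the SBP reduction was 7.8 mmHg" and that "ICC value was 0.05". From these it concludes: "to detect a possible absolute difference of 5.0 mmHg with 90% power and alpha 0.05, we need 228 patients in each arm". It then inflates that number: "By allowing for a 20% attrition rate and a design effect of 2.45, the total sample size is estimated as 3352". The product shown multiplies 228 by a design effect of 2.45, by five groups (control plus four intervention subgroups) and by 1.2 for attrition, and "this translates into 56 patients per community".

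The section on selection and randomization of communities uses the same number: "step 4 randomly selects 56 patients diagnosed with hypertension from the communities selected". The study design section has 12 control and 48 intervention communities, and gives the comparison of control with at least four intervention subgroups as the reason for the uneven split. The withdrawal section says that participants who leave are not replaced. The article does not say which cluster size underlies 2.45.

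**The concern.** A design effect is tied to a cluster size. Here the cluster size is an output of the calculation (56), but the design effect that went in belongs to a much smaller cluster (30). The clustering penalty is therefore understated for the trial as designed. Multiplying by 1.2 also does not restore the required number after a fifth of patients are lost.

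Both errors push the same way: each group carries less information than the derivation claims. At stake is the published justification for the control v subgroup contrasts, which are the stated reason for allocating communities 12:48.

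**Working it through.** **Inputs (Study sample size, Study design and settings):** difference 5.0 mmHg, SD 7.8, ICC 0.05, power 90%, alpha 0.05, attrition 20%, design effect 2.45, five groups, 60 communities (12 control, 48 intervention), 56 patients per community. Assumptions: two-sided test, equal cluster sizes.

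**1. The plan's total.** 2.45 × 228 × 5 × 1.2 = 3351.6, and 3352/60 = 55.9. So 3352 and 56 follow from the plan's own factors.

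**2. Design effect.** The formula is DE = 1 + (m − 1) × ICC.
- Solving for 2.45: m = 1 + 1.45/0.05 = 30.
- At 56 enrolled: 1 + 55 × 0.05 = 3.75.
- At 56 × 0.8 = 44.8 analysed: 1 + 43.8 × 0.05 = 3.19.

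Thirty is not the number of completers either: 30/56 would mean 46% loss.

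**3. Attrition.** The derivation needs 2.45 × 228 × 5 = 2793 completers. Enrolling 3352 leaves 3352 × 0.8 = 2682, or 96%. The correct inflation is 2793/0.8 = 3491.25, so 3492.

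**4. Effective sample size per group of 12 whole communities.**
- Attrition error alone: 12 × 44.8/2.45 = 219.4.
- Both errors: 12 × 44.8/3.19 = 168.5, and 168.5/228 = 74%.
- No loss at all: 12 × 56/3.75 = 179.2.

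Larger communities would not realistically close the gap. With 12 communities the effective size cannot exceed 12/0.05 = 240, and solving 12m/(0.95 + 0.05m) = 228 gives m = 361 completers per community.

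**5. Does 228 follow from its inputs?** n per arm = 2 × (7.8 × 3.2415/5)² = 51.1, so 52. One-sided testing gives 42, and a Bonferroni correction for four comparisons gives 70. No variant tried gave 228; the largest was 193. To obtain 228, the SD would have to be 5 × √114/3.2415 = 16.5, or the difference 7.8 × 3.2415/√114 = 2.37 mmHg.

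**6. Power to detect 5.0 mmHg with the corrected factors** (44.8 analysed per community, effective size 168.5 per 12 communities):

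| Contrast | SD 7.8 (stated) | SD 16.5 (implied by 228) |
|---|---|---|
| 12 v 12 communities | above 99.9% | 79.6% (75.9% with t, 22 df) |
| 12 v 48 communities, pooled | above 99.9% | 94.1% (93.4% with t, 58 df) |
| Control v subgroup of patients split within the 48 communities | above 99.9% | 90% (87–89% with t on 22–58 df) |

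The last row has 44.8/4 = 11.2 completers of each subgroup per community, DE = 1 + 10.2 × 0.05 = 1.51, and an effective subgroup size of 48 × 11.2/1.51 = 356. The control group stays at 168.5. At SD 16.5 the attrition error alone takes a 12 v 12 contrast only from 90% to 88.9%.

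**The case against.** The tempting stronger reading is that the promised 90% power is not delivered. The documents do not support it. On the stated difference and SD only about 52 per arm are needed, and with every correction applied a 12 v 12 contrast still has power above 99.9%. The 76–80% figure requires 228 to be the true requirement, hence an SD near 16.5 that appears nowhere in the article. This objection stands, so the power loss can only be stated conditionally.

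The 12 v 12 figures also assume that each subgroup consists of 12 whole communities. The 12:48 split makes that plausible, but the article does not say it. Communities are randomised only to control or intervention, and the sample-size section speaks of assigning patients to subgroups. If subgroups are formed within communities, the shortfall nearly disappears even at SD 16.5, and the cap of 240 binds only the control group. This also stands.

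Finally, the pooled intervention v control comparison, which matches the study hypothesis, stays above 90% even in the unfavourable case, and the attrition error is minor. Both lower the severity. None of this repairs the two factors: 2.45 and 1.2 do not match the design whichever SD is right.

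**Conclusion.** The derivation is wrong as written. The design effect contradicts the trial's own ICC and cluster size, and the attrition factor is slightly too small. With five groups of 12 communities, the effective size is about 168.5 per group, 74% of the stated 228. Nearly all of the shortfall comes from the design effect.

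The consequence for power is open until 228 is reconciled with the 5.0 mmHg difference and the SD of 7.8. It ranges from none (SD 7.8) to about 76–80% for a whole-community subgroup contrast if 228 is right, with about 93–94% for the pooled contrast. If patients are split within communities, the subgroup figure in that case is about 87–90%. These results rest on ICC 0.05, 20% loss spread evenly, equal cluster sizes and two-sided 5% tests without multiplicity adjustment. The point merits correction but does not show that the trial is underpowered.

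**What to change.** Keep 60 communities and 56 patients per community, and rewrite the sample-size paragraph:

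- Use the design effect at the analysed cluster size (3.19 at 44.8 completers), and say which cluster size it refers to.
- Replace the factor 1.2 by 1/(1 − 0.20).
- Reconcile 228 with the stated difference and SD, by correcting whichever figure was misreported.
- State whether the four subgroups are formed from whole communities or from patients within communities.
- Then restate power separately for the subgroup v control contrasts and for all intervention v control.

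The 76–80% figure should not be printed beside an SD of 7.8, since that would create a new contradiction. The cost is a text change only. The downside is that the stated subgroup power may become less favourable.
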